#### Primary outcome measure

The AHA will be the primary outcome measure and it will be evaluated at every time point. The AHA assesses how effectively the more impaired hand is used in bimanual activities [25, 39, 40]. The spontaneous use is evaluated during a semi-structured play session with standardized toys requiring bimanual handling. The performance is video recorded and scored afterwards. Given the age range of the participants of this study, the School Kids AHA will be used, scored with version 5.0. This version includes 20 items that are scored form 0 (‘does not do’) to 4 (‘effective use’), and it has been shown to be valid and reliable [25, 40].

#### Secondary outcome measures

##### UL assessment at body function and structure level

UL motor impairments will be assessed at every time point and include (1) passive range of motion (pROM), (2) muscle tone, (3) muscle strength and (4) grip strength. All assessments will be executed following a valid and reliable protocol in children with uCP defined by Klingels et al. [34]. A universal goniometer will be used to evaluate pROM of the shoulder (flexion, abduction, internal and external rotation) elbow (flexion and extension), forearm (pronation and supination) and wrist (flexion and extension). Muscle tone will be assessed using the Modified Ashworth Scale [41] for muscle groups of the shoulder (extensors, adductors, abductors, external and internal rotators), elbow (flexors, extensors and pronators), wrist (flexors and extensors) and hand (finger flexors and thumb adductors). Muscle strength will be evaluated using manual muscle testing [42] according to the 8-point ordinal scale of the Medical Research Council. Muscle groups of the shoulder (flexors, adductors and abductors), elbow (flexors, extensors, supinators and pronators) and wrist (flexors and extensors) will be assessed. Finally, maximum grip strength will be assessed using the Jamar® hydraulic hand dynamometer (Sammons Preston, Rolyan, Bolingbrook, IL, USA). The mean of three maximum contractions will be calculated for both hands. Furthermore, to calculate the Static Fatigue Index as described by Severijns et al. [43], a 30 s sustained contraction will be performed with a digital hand grip module (E-link, Biometrics Ltd., Newport, UK). The sustained contraction will be evaluated at time points T1, T2 and T3.

##### UL assessment at activity level

UL activity assessments will include measures of unimanual capacity, bimanual performance and manual ability.Melbourne Assessment 2

The Melbourne Assessment 2 (MA2) is a criterion-referenced test designed for children with uCP aged 2.5 to 15 years [44]. This scale measures unimanual capacity and has been proven valid and reliable for this population [45]. The MA2 assesses UL movement quality by means of 14 unimanual tasks, including 30 movement scores grouped across four subscales: range of motion, accuracy, dexterity and fluency. Each sub-score is converted into a percentage. The performance is video recorded and subsequently scored. The MA2 will be measured at every time point.Jebsen-Taylor hand function test

The Jebsen-Taylor hand function test (JTHFT) measures movement speed during six unimanual tasks [46, 47]. As similar to other studies, a modified version for children with uCP will be used. In the modified version, the writing task is removed, and the time to carry out each teak is reduced from 3 to 2 min to avoid frustration [16, 48]. This test uses standardized material and time needed to perform the task is directly recorded. Practice trials are not allowed. The JTHFT has established construct, content validity and reliability [16]. This test will be evaluated at every time point.Tyneside pegboard test

The Tyneside pegboard test will be used to quantify unimanual and bimanual dexterity. The Tyneside pegboard test is an adapted 9-hole pegboard test, where two adjacent boards are placed next to each other. In the unimanual task, the child moves the pegs from one board to the other using first the less impaired and then the more impaired hand, recorded separately. The unimanual task will be repeated three times with different peg sizes (large, medium and small). For the asymmetric bimanual task, the large pegs will be picked up from one board, passed through a hole in a Perspex® divider placed between the boards, and inserted into the second board with the other hand. Children will be instructed to perform the tasks as fast as possible without paying attention to the order of lifting and inserting the pegs. The test is electronically timed and results are outputted using a custom-written software (Institute of Neuroscience, Newcastle University, Newcastle upon Tyne, United Kingdom) [49]. This test will be evaluated at T1, T2 and T3.ABILHAND-Kids Questionnaire

The ABILHAND-Kids questionnaire is developed to assess manual ability in children with CP aged 6 to 15 years. It comprises 21 mainly bimanual daily activities. The difficulty experienced by the child to perform the required tasks is rated on a 3-point ordinal scale by the parents [50]. A Rash model was used to validate the ABILHAND-Kids questionnaire and its reliability and reproducibility over time has been shown [50]. This questionnaire will be evaluated at every time point.Children’s Hand-use Experience Questionnaire

The Children’s Hand-use Experience Questionnaire (CHEQ) is an online questionnaire that captures the child’s experience of using the more impaired hand during bimanual activities (available online at http://www.cheq.se). Parents will answer 29 questions to describe how independently the activities are performed. Each question has three sub-questions, on a 4-point rating scale, measuring (i) hand use, (ii) time use in comparison to peers and (iii) experience of feeling bothered when doing the activity. A Rash model was used to validate the CHEQ and its reliability has been shown [51]. This questionnaire will be evaluated at every time point.

##### Three-dimensional motion analysis

Upper Limb Three-Dimensional Motion Analysis (UL-3DMA) will be conducted at T1, T2 and T3. A custom-made chair with foot and back-support is used to perform the measurements in a standardized sitting position. A total of 17 reflective markers (14 mm diameter) are attached to the trunk, acromion, upper arm, forearm, and hand. Next, several static calibration trials are conducted to identify anatomical landmarks of interest, following the guidelines of the International Society of Biomechanics [52]. The movement protocol contains eight tasks: three reaching tasks (forwards, RF; upwards, RU; sideways, RS), two reach-to-grasp tasks (grasp a sphere, RGS; grasp a vertical cylinder, RGV) and three daily-life activities mimicking tasks (hand-to-head, HTH; hand-to-mouth, HTM; hand-to-shoulder, HTS). Each task was performed four times within two trials, resulting in eight movement repetitions per task. Tasks were executed with the impaired UL at self-selected speed. Each task is started in upright sitting with 90° of hip and knee flexion, with the impaired hand on the ipsilateral knee. This protocol has been proven reliable in children with uCP [53]. To record motion, 12 to 15 Vicon infrared cameras (Oxford Metrics, Oxford, UK) sampling at 100 Hz will be used to capture the UL movement patterns. Offline data processing will be performed with Vicon Nexus software (version 1.8.5, Oxford Metrics, Oxford, UK) and consists of a Woltring filtering routine with a predicted mean squared error of 10 mm^2^ [54], gap filling, and selection of the movement cycles (start (hand on ipsilateral knee) and end of each movement cycle). Task end-point is defined as follows: (1) touching the spherical object with the palm of the hand (RF, RU and RS), (2) grasping (sphere (RGS) or vertical cylinder (RGV)), and (3) touching different parts of the body (top of the head (HTH), mouth (HTM) or contralateral shoulder (HTS)). To avoid start and stop strategies of the child, only the middle two repetitions of each trial will be analysed, resulting in four analysed movement repetitions per task. Lastly, we time-normalize the movement cycles (0–100%) and calculate the root mean squared error (RMSE) of the kinematic angles of each cycle to compare it to the mean of the remaining 3 cycles (per task). As such, we retain the 3 cycles with the lowest RMSE for further analysis, which represent the most reliable movement patterns. The open source software ULEMA v1.1.9 [53, 55, 56] will be used to calculate the kinematics of five joints with a total of 13 angles: trunk (rotation, lateral flexion and flexion-extension), scapula (tilting, pro-retraction and rotation), shoulder (rotation, elevation plane and elevation), elbow (flexion-extension and pro-supination) and wrist (flexion-extension and ulnar-radial deviation). Spatiotemporal parameters, joint kinematics and summary indices will be calculated and used for statistical analysis.

##### Assessment of participation and quality of life

Participation and quality of life of the children will be evaluated at time points T1 (before) and T3 (follow-up).Participation

To evaluate changes in participation, parents will be asked to fill in the short version of the Life Habits (Life-H) questionnaire. This short version contains 64 items on life habits such as nutrition, fitness, personal care, mobility and community life. It uses a scoring system ranging from 0 (total impairment) to 9 (optimal participation) [57]. The Life-H has a good validity and a good internal consistency and a moderate test-retest reliability [4].Quality of life

To evaluate changes in quality of life, parents will be asked to fill in the Cerebral Palsy Quality of Life Questionnaire (CPQOL). The CPQOL is a condition-specific measure, designed for children with CP, that evaluates the well-being of children across seven areas of a child’s life: social well-being and acceptance, functioning, participation and physical health, emotional well-being, access to services, pain and impact of disability and family health [58]. In this study, the primary caregiver-proxy report, which contains 66 items, version for children aged 4–12 years will be used. The CPQOL has a high internal consistency and good test-retest reliability [58].

### Neurological predictors

A 3.0-T system (Achieva, Philips Medical Systems, Best, The Netherlands) will be used for image acquisition. The medical imaging protocol will include (1) structural magnetic resonance imaging (sMRI) for anatomical characterization (i.e. lesion timing, location and extent), (2) diffusion weighted imaging (dMRI) to evaluate white matter structural connectivity and (3) resting-state functional MRI (rsfMRI) analysing functional connectivity. To familiarize the children with the scanner situation, they will follow a training session prior to the scan, which consists of performing scan-related tasks similar to the protocol described by Theys et al. [59].

#### Structural MRI

Structural images will be acquired using three-dimensional fluid-attenuated inversion recovery (3D FLAIR) with following parameters: 321 sagittal slices, slice thickness = 1.2 mm, slice gap = 0.6 mm, repetition time = 4800 ms, echo time = 353 ms, field of view = 250 × 250 mm^2^, 1.1 × 1.1 × 0.56 mm^3^ voxel size, acquisition time = 5 min. In addition, magnetization prepared rapid gradient echo (MPRAGE) will be acquired with following parameters: 182 slices, slice thickness = 1.2 mm, slice gap = 0 mm, TR = 9.7 ms, TE = 4.6 ms, FOV: 250 × 250mm^2^, 0.98 × 0.98 × 1.2 voxel size, acquisition time = 6 min. Also, T2-weighted images will be obtained with following parameters: slice thickness 4 mm, TR = 6653 ms, TE = 100 ms, FOV = 250 × 250 mm2, 0.94 × 0.94 × 1.0 voxel size, acquisition time = 3 min.

#### Diffusion weighted imaging

Diffusion weighted images (dMRI) will be acquired using a single shot spin echo sequence with the following parameters: slice thickness = 2.5 mm, TR = 8700 ms, TE = 116 ms, number of diffusion directions = 150, number of sagittal slices = 58, voxel size = 2.5 × 2.5 × 2.5 mm^3^, acquisition time = 18 min. Implemented b values are 700, 1000, and 2800 s/mm^2^, applied in 25, 40, and 75 uniformly distributed directions, respectively. In addition, 11 non-diffusion weighted images will be obtained. dMRI data will be pre-processed and analysed in ExploreDTI toolbox, version 4.8.6 (available for download at http://www.exploredti.com/download.htm). Diffusion metrics, such as fractional anisotropy and mean diffusivity of white matter tracts of interest (i.e. corpus callosum, corticospinal tract, medial lemniscus superior, thalamic radiations) will be calculated for both hemispheres using manually drawn regions of interest.

#### Resting state functional MRI

Resting-state function MRI (rsfMRI) images will be acquired using a T2*-weighted gradient-echo planar imaging sequence with the following parameters: TR = 1700 ms; TE = 30 ms; matrix size = 64 × 64; FOV = 230 mm; flip angle = 90°; slice thickness = 4 mm; no gap; axial slices = 30; number of functional volumes = 250; acquisition time = 7 min. Participants will be instructed to stay at rest, with eyes open, not to fall asleep and to think of nothing in particular. rsfMRI will be pre-processed with Statistical Parametric Mapping version 12 (SPM12) software [65]. Functional connectivity analysis will be computed with the CONN toolbox v17b [66, 67]. Correlation coefficients (indicating high versus low functional connectivity) will be determined among cortical and subcortical regions of interest within the sensorimotor network in the affected and less-affected hemisphere, which are relevant for UL function. Furthermore, the cortical areas involving the mirror neuron system will also be explored.

#### Transcranial magnetic stimulation

Single-pulse Transcranial Magnetic Stimulation (TMS) will be conducted to assess the CST wiring pattern. This assessment will be conducted only in the children with uCP who were eligible for this test, i.e. no implants in the body (metals, pacemaker, ventriculoperitoneal shunt) and no seizures within the last 2 years [68]. TMS will be performed using a MagStim 200 Stimulator (Magstim Ltd., Whitland, Wales, UK) equipped with a focal 70 mm figure-eight coil and a Bagnoli electromyography (EMG) system with two single differential surface electrodes (Delsys Inc., Natick, MA, USA). A Micro1401–3 acquisition unit and Spike software version 4.11 (Cambridge Electronic Design Limited, Cambridge, UK) were used to synchronize the TMS stimuli and the EMG data acquisition. Motor Evoked Potentials (MEPs) will be bilaterally recorded, using single differential surface EMG electrodes attached on the muscles adductor pollicis brevis of both hands.

We will follow the protocol defined by Staudt et al. [69]. During the TMS assessment, the children will wear a cap that allows to create a coordinate system used to find the optimal point to stimulate (hotspot) in a systematic way for all participants. The hotspot and the resting motor threshold (RMT) are identified by starting the stimulation intensity at 30% and increasing it in steps of 5%. The RMT is defined as the minimum intensity needed to obtain 5 out of 10 MEP of at least 50 μV in the correspondent muscle. After hotspot and RMT identification, 10 MEPs will be collected at an intensity of 120% the RMT. The TMS session is carried out as follows: first, stimulation starts in the less-affected hemisphere, where contralateral projections to the contralateral hand are searched and identified. Second, stimulation in the less-affected hemisphere continues up to 100% of the maximum stimulator output to search for possible ipsilateral projections to the ipsilateral (more impaired) hand. Third, we stimulate the affected hemisphere to search for possible contralateral projections to the contralateral hand (more impaired hand). If only contralateral MEPs from each hemisphere are found, the child will be categorized as having a contralateral CST wiring pattern. If MEPs in the more impaired hand are identified from both hemispheres, the child will be categorized as having a bilateral CST wiring pattern. Lastly, if MEPs in the impaired hand are only found when stimulating the less-affected hemisphere (ipsilateral hemisphere), the child will be categorized as having an ipsilateral CST wiring.

### Statistical analysis

Descriptive statistics of the outcome variables will be reported by using means and standard deviations or median and interquartile ranges, depending on their data distribution. Normality will be checked with the Shapiro-Wilk test and histograms will be checked for symmetry. Mixed models will be used to study changes after the intervention over time. By using random effects, these models are able to correct for the dependency among repeated observations. Furthermore, these models deal with missing data offering valid inferences, assuming that missing observations are unrelated to unobserved outcomes [70]. Based on the data distribution, linear (parametric) or generalized (non-parametric) linear mixed models will be used. Changes over time will be tested between groups, by analysing treatment-time interactions. In case of such a significant treatment-time interaction, changes over time will be investigated separately in each group. Significant time trends will be further investigated with pairwise post hoc tests to compare time points. Additionally, the effect size will be calculated using the Cohen’s d formula (small, 0.2–0.5; medium, 0.5–0.8, and large > 0.8) [71]. Both clinical (age, baseline AHA score, sensory function, mirror movements) and neurological predictors (brain lesion characteristics, structural and functional connectivity and CST wiring) will be included as covariates in the models for the primary outcome measure, together with their interaction with time and treatment to evaluate their potential confounding factor. The two-sided 5% level of significance will be used. All statistical analyses will be performed using SAS version 9.2 (SAS Institute, Inc., Cary, NC) and SPSS Statistics for Windows version 24.0 (IBM Corp. Armonk, NY: IBM Corp.).

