### Hypothesis

The RCT will address the following research hypotheses:mCIMT, in combination with AOT, augments the treatment effects immediately after intervention and results in improved UL function with longer retention beyond mCIMT alone.The combination of neurological predictors, i.e. neuroanatomical brain lesion characteristics, structural and functional connectivity and CST wiring pattern, better determines treatment response compared to clinical predictors.Children with a bilateral and ipsilateral CST wiring respond less to the treatment compared to children with contralateral CST wiring in both intervention groups.In children with more lesions or disturbed connectivity in the areas involving the mirror neuron system, AOT is not as effective as in those with less lesions in this area.

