### Sample size

Sample size estimate is based on the primary endpoint, which is defined as the immediate effect of the intervention on the primary outcome measure, i.e. bimanual performance measured with the Assisting Hand Assessment (AHA). The smallest detectable difference has been reported to be 5 AHA units [24]. A previous intervention study of intensive therapy in children with uCP [6], reported a standard deviation of 5.5 AHA units, which would translate into an effect size of 0.9. With this effect size, an alpha-level of 0.05, and a statistical power of 0.80, a sample size of 21 children is needed in each group to detect a difference equal to or larger than the smallest detectable difference of 5 AHA units between groups [24, 25]. Sample size estimates were calculated with G*Power [26, 27].

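### The primary endpoint is one between-group contrast (immediate AHA effect), but the stated analysis tests it only as one component of a treatment-time interaction, with within-arm follow-up

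*Protocol article*

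**What the plan says.** The Sample size section fixes both the endpoint and the comparison: "Sample size estimate is based on the primary endpoint, which is defined as the immediate effect of the intervention on the primary outcome measure". The trial is sized "to detect a difference equal to or larger than the smallest detectable difference of 5 AHA units between groups". By the Study design section, the immediate effect is the change from T1 (within 4 days before the camp) to T2 (within 4 days after it).

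The Primary outcome measure section adds: "The AHA will be the primary outcome measure and it will be evaluated at every time point". Table 1 confirms four AHA assessments, T0 to T3. The first hypothesis has two parts, namely that adding AOT "augments the treatment effects immediately after intervention and results in improved UL function with longer retention beyond mCIMT alone".

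The Statistical analysis section sets out this sequence:

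1. A mixed model in which changes over time are compared between groups through treatment-time interactions. Neither the time points in the model nor the coding of time is given.
2. "In case of such a significant treatment-time interaction, changes over time will be investigated separately in each group".
3. Where a time trend is significant, post hoc pairwise comparisons of time points.

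Cohen's d is also planned, without saying for which comparison.

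**The concern.** The quantity that was powered and the quantity that is tested are not the same. The powered quantity has one degree of freedom: the difference between arms in T1-to-T2 change. The tested quantity, as far as the text shows, is a joint hypothesis about all changes over time. A significant result says that the arms' profiles differ somewhere, not that they differ immediately after the camp.

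The natural next step would be to ask, between arms, where the difference lies. The stated next steps look inside each arm and compare time points instead. Both arms receive 54 hours of intensive therapy, so both may well improve, and a within-arm gain says little about what AOT adds.

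At stake is the trial's main conclusion. Followed as written, the plan could report a positive primary result that comes from the 6-month visit. It also specifies no estimate or interval for the difference on which the sample size rests, and no specific between-arm comparison for retention.

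**Working it through.** **Inputs from the document.** Target difference 5 AHA units, SD 5.5, effect size 0.9, alpha 0.05 (two-sided by the Statistical analysis section), power 0.80, 21 per group, AHA at four time points.

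**Assumptions not in the document.** Compound symmetry across visits, and 5.5 read as the SD of change. The text does not say whether 5.5 refers to scores or to changes.

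**Step 1: the plan's own figure.** 5/5.5 = 0.909. A two-sided two-sample t-test at 80% power needs 20.0 per group for d = 0.909 and 20.4 for d = 0.9, so 21 after rounding up. A one-sided test would need 16. The stated 21 is therefore a two-sided figure for a single contrast. With 21 per arm the noncentrality is 0.909 × √(21/2) = 2.95 on 40 df, and power is 0.82.

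**Step 2: which time points does the interaction cover?** The article does not say. Pairwise tests of time points after a significant trend make sense only with more than two. Retention needs T3, and no other analysis is given for it. I therefore take two cases: T0 to T3 (3 df) and T1 to T3 (2 df).

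**Step 3: an effect at T3 only.** Let δ_t be the true group difference at visit t. The noncentrality of the interaction is λ = (n/2) × Σ(δ_t − mean δ)² / σ_w², with σ_w² = 5.5²/2 = 15.125 and n = 21.

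For T0 to T3 with δ = (0, 0, 0, 5): the mean is 1.25, the sum of squares is 3 × 1.5625 + 14.0625 = 18.75, and λ = 10.5 × 18.75/15.125 = 13.02.

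For T1 to T3 with δ = (0, 0, 5): the sum of squares is 16.67 and λ = 11.57.

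The table gives the probability of a significant interaction when the T2 difference is zero. The first figure in each cell uses the mixed-model denominator df (120 or 80), the second a Hotelling-type df (38 or 39).

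| Difference at T3 only | T0-T3, 3 df | T1-T3, 2 df | T1-to-T2 contrast, 1 df |
|---|---|---|---|
| 5 units | 0.86 / 0.83 | 0.86 / 0.84 | 0.05 |
| 4 units | 0.66 / 0.62 | 0.66 / 0.65 | 0.05 |
| 3 units | 0.40 / 0.38 | 0.42 / 0.40 | 0.05 |

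Leaving T0 out, or changing the df method, moves these figures by 4 percentage points at most.

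**Step 4: power for a true 5-unit effect at T2** (Hotelling-type df).

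| Pattern | T0-T3, 3 df | T1-T3, 2 df | T1-to-T2 contrast |
|---|---|---|---|
| T2 only | 0.83 | 0.84 | 0.82 |
| Halved by T3 | 0.79 | 0.72 | 0.82 |
| Sustained to T3 | 0.93 | 0.84 | 0.82 |

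Depending on the pattern, the interaction gains or loses a little. The problem is specificity, not power.

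**Step 5: sensitivity to the SD.** If 5.5 is the SD of scores, the result depends on the correlation ρ between visits. For ρ = 0, 0.5 and 0.8, the 1-df contrast has power 0.53, 0.82 and 0.995. The 3-df interaction (Hotelling-type df) is then significant for a 5-unit T3-only difference with probability 0.51, 0.83 and 0.998.

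**The case against.** **The immediate effect is tested between groups.** A reader might infer from the within-arm follow-up that no between-group test exists. The document does not support that. The sentence before the one quoted announces a between-group test of changes over time, and that test contains the T1-to-T2 change. This part of the objection stands. What is lacking is a test specific to that change.

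**The within-arm step is gated.** A reader might also infer that it would produce conflicting arm results in about half of trials. With equal true gains of 2.5 or 3 units in both arms, paired tests (n = 21, SD 5.5) have power 0.51 and 0.66. Discordance, 2p(1 − p), is then 0.50 and 0.45. But the plan takes this step only after a significant interaction. With equal gains, a significant interaction together with discordant T1-to-T2 tests occurs in about 3.5% of simulated trials. Nor does the article say that significance in one arm alone will be read as a difference between arms.

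**The T3-only scenario contains a true AOT effect.** This is correct, and retention is part of the first hypothesis. The error is to attribute a late difference to the immediate endpoint, not to declare an inert treatment effective. No immediate effect followed by 5 units at 6 months is also an extreme pattern, which is why 3 and 4 units are shown as well.

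**The model might hold only T1 and T2.** The interaction would then be exactly the 1-df primary contrast. The article does not exclude this in words, but its pairwise time-point tests and its retention hypothesis make it implausible.

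**An article condenses.** Time points, contrasts and intervals may stand in a fuller plan, and a mixed model with treatment-time terms can produce them. Silence alone would be no finding. Here, however, a sequence of tests is stated, and it does not lead to the stated endpoint.

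**Conclusion.** The concern holds as a mismatch between the endpoint and the stated analysis. The sample size rests on one between-group contrast, the immediate AHA effect. The analysis reaches it only through a treatment-time interaction, and what follows a significant result is within-arm. No step specifically tests or estimates the group difference at T2, or at T3.

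The size is a risk of misattribution: roughly 83-86%, 62-66% or 38-42% for a T3-only difference of 5, 4 or 3 units, against 5% for a direct contrast. These figures rest on compound symmetry, a change SD of 5.5, 21 per arm with complete data, and a model with at least T1, T2 and T3. I claim neither a power loss nor an inflated error rate when AOT has no effect at any time.

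**What to change.** In the Statistical analysis section, name one primary test: the between-group difference in T1-to-T2 AHA change, or in AHA at T2 adjusted for AHA at T1. Estimate it from the mixed model as a single 1-df contrast with a 95% CI, at two-sided 0.05, and do not make it depend on the interaction. State which time points enter the model.

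Make the between-group contrast at T3 a secondary analysis for retention, and report within-arm changes descriptively. Testing T3 only if T2 is significant is an option, not a necessity.

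The cost is a few sentences, with no new data and no more children. N = 42 already fits this test (power 0.82 if 5.5 is the SD of change). The Sample size section should say whether it is.

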Several studies investigating the efficacy of mCIMT in children with uCP, have reported a large inter-individual variability in treatment response [6, 15–17]. These studies have suggested that children with poorer UL function at baseline may benefit more from mCIMT. Moreover, some studies have investigated whether neurological factors, e.g. corticospinal tract (CST) wiring pattern or brain lesion characteristics, may determine treatment response. Despite the increasing number of studies investigating this research question, results are still contradicting. Two studies hypothesized that in children with an ipsilateral wiring pattern, constraining the less impaired UL may drive down primary motor cortex activity controlling both ULs, and thus possibly preventing improvement of the more impaired UL [18, 19]. In contrast, Islam et al. reported improved UL function after mCIMT irrespective of the CST wiring patterns [20], highlighting the importance of considering other relevant neurological factors. Interestingly, a few studies have already investigated the potential role of structural and functional connectivity in predicting treatment response, reporting that especially children with more affected structural and functional connectivity improved after mCIMT [21–23]. Notwithstanding the valuable insights reported by these studies, their sample sizes were relatively small. Moreover, the combination of structural and functional connectivity with CST wiring pattern to predict treatment outcome in children with uCP has not yet been investigated.

Furthermore, UL function has thus far mostly been evaluated using clinical scales on body function and activity level according to the International Classification of Functioning, Disability and Health (ICF) model. Whilst these clinical scales have been proven valid and reliable, they lack the information on anatomical motions at the single joint level. Moreover, they do not capture the complexity of UL motion, involving the coordinated interaction of movement sequences of multiple degrees of freedom. Hence, a more quantitative assessment, such as three-dimensional movement analysis (3DMA), may provide a better understanding of the changes that occur at the joint level and thus contribute to further insights on the effectiveness of UL treatment programs in children with uCP.

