### Randomisation

Children will be assigned using stratified random sampling. Before intervention (T1), children will be first stratified according to the House Functional Classification Scale (4–5 vs. 6–7), age (6-9y vs. 10–12 y), and the type of CST wiring pattern (contralateral, bilateral and ipsilateral) assessed by Transcranial Magnetic Stimulation (TMS) to maximize homogeneity and minimize group differences at baseline. A permuted block design of two will then be used, created by a computer random number generator to randomize the participants to the mCIMT+AOT or mCIMT alone group within each stratum. Randomization will be performed by an independent person who is not involved in the selection procedure and cannot access the clinical information of the children.

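### HFC, a stratification factor, is missing from the listed covariates, and the article does not say that the main treatment-by-time test is adjusted for the three randomisation strata

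*Protocol article*

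**What the plan says.** The Randomisation section stratifies children by HFC (4–5 against 6–7), age (6–9 against 10–12 years) and CST wiring (three classes), then uses permuted blocks of two within each stratum. The stated aim is "to maximize homogeneity and minimize group differences at baseline".

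The Statistical analysis section tests the AOT effect as a treatment-time interaction in a mixed model. That sentence names no covariates. Later the section lists "Both clinical (age, baseline AHA score, sensory function, mirror movements) and neurological predictors (brain lesion characteristics, structural and functional connectivity and CST wiring", and places these variables as covariates in the models for the primary outcome, with their interactions with time and treatment, in order to examine confounding. HFC does not appear. Age, CST wiring and baseline AHA do.

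On whether these factors predict response, the Background reports that "children with poorer UL function at baseline may benefit more from mCIMT". The Hypothesis section expects less response with bilateral or ipsilateral wiring in both groups. Neither gives a figure.

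**The concern.** When randomisation balances a factor that predicts the outcome, the true sampling variance of the group difference falls. An analysis that ignores the factor leaves its variance in the residual, so the reported standard error is larger than the design warrants. The test then runs below its nominal level and the interval is too wide.

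Two features of the text raise this. HFC is a design factor that the explicit covariate list leaves out. Age and CST wiring are listed, but together with treatment interactions. In such a model the treatment-time term is the effect at one reference value of each covariate, not the overall AOT effect. So no model is clearly stated that gives the overall effect adjusted for the strata. At stake is some precision in a trial of 42 children.

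**Working it through.** **Inputs.** From Sample size: "The smallest detectable difference has been reported to be 5 AHA units"; a previous study "reported a standard deviation of 5.5 AHA units"; "an alpha-level of 0.05, and a statistical power of 0.80"; 21 children per group. From Statistical analysis: "The two-sided 5% level of significance will be used". From Randomisation: 2 × 2 × 3 = 12 strata, blocks of two. Assumed, because the article gives no figure: R², the share of the variance of T1–T2 AHA change that the strata explain. For the simulations: HFC and age bands of equal size, CST classes split 40/30/30, no dropout.

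**Step 1: the plan's own figure.** d = 5/5.5 = 0.909, given as 0.9. A two-sided two-sample t-test at d = 0.9 needs n = 20.39, so 21 per group, with power 0.812; at d = 0.909 the power is 0.820. The stated sample size reproduces and does not depend on the strata.

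**Step 2: when does leaving out a stratum matter?** The treatment-time contrast is within child, so a factor that shifts only the AHA level cancels. In simulation, a 20-unit HFC difference in level with no effect on change gave a mean standard error of 1.687 without HFC and 1.686 with it. An HFC effect on change of 2.5 units gave 1.737 against 1.691 (1.737/1.691 = 1.03). An effect of 5 units gave 1.863 against 1.686 (1.863/1.686 = 1.10). Only prediction of change matters.

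**Step 3: size if no stratum is in the model.** With full balance within strata, the standard error is inflated by 1/√(1 − R²):

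- R² = 0.05: 1/√0.95 = 1.026
- R² = 0.10: 1/√0.90 = 1.054
- R² = 0.20: 1/√0.80 = 1.118

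Under the same idealisation, the type I error of the unadjusted test is 2(1 − Φ(1.96/√(1 − R²))), which is 0.039 at R² = 0.10 and 0.028 at 0.20. With 42 children in up to 12 cells some blocks stay unfinished. Simulation with 8,000 runs per scenario gives 0.041 and 0.034, still conservative but less so.

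**Step 4: power for 5 units, no strata against all three as main effects (same simulation).**

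| R² | unadjusted | adjusted | difference |
|---|---|---|---|
| 0 | 0.814 | 0.805 | −0.009 |
| 0.05 | 0.815 | 0.821 | +0.006 |
| 0.10 | 0.822 | 0.845 | +0.023 |
| 0.20 | 0.827 | 0.881 | +0.054 |

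**Step 5: age and CST wiring already in the model.** If HFC, age and CST each explain 10% of change variance, the mean 95% interval width is 6.85 units with no strata, 6.17 with age and CST, and 5.78 with all three. Age and CST recover (6.85 − 6.17)/(6.85 − 5.78) = 0.68/1.07, about 64% of the excess. The remaining excess is 6.17/5.78 = 1.07, or 7%. If HFC explains nothing, adding it to age and CST changes the width from 6.88 to 6.90. Baseline AHA is also listed and probably carries part of the HFC information; this was not simulated.

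**The case against.** The strongest reply is that the article puts age, CST wiring and baseline AHA into the models for the primary outcome, with the time interactions that adjustment needs. A reader might infer that all three strata are left out, or that age and CST belong only to a separate predictor model. The text supports neither: no separate predictor model is named. What remains is HFC's absence and the silence on which model supplies the main test.

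Second, the Background hint concerns baseline function, which baseline AHA already represents, and the same section calls the evidence on wiring contradictory. This stands. Only what the strata add beyond baseline AHA counts, and that is unknown.

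Third, the error is conservative, planned power of 0.80 is met without adjustment, and the stated purpose of stratifying is baseline balance, which it serves whatever the model. This also stands. A reader might say that the plan forfeits a power gain it had counted on, but the sample size calculation claims none.

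Fourth, a condensed article commonly leaves the exact fixed effects to a fuller document. This limits the point but does not remove it: the article chose to name its covariates one by one, and that list omits a design factor.

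**Conclusion.** The point holds as a conditional one. HFC is absent from the covariate list, and the article does not say that the main treatment-by-time test is adjusted for the strata. It does not follow that the intervals are too wide as a matter of fact. They are too wide only if the strata predict AHA change beyond baseline AHA, for which the article offers suggestions but no number.

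If they do, the interval is too wide by about 3%, 5% or 12% at an assumed R² of 5%, 10% or 20% with no stratum in the model, and by less if age, CST wiring and baseline AHA are in it. The realistic power gain is about 1 to 5 points, against a loss of about 1 point if the strata explain nothing. The treatment estimate is not biased, false positives are not inflated, and the sample size of 21 per group is unaffected.

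**What to change.** State one primary model for the AOT effect on AHA at T2. Include HFC stratum, age stratum and CST class as main effects, each also by time if time points are modelled jointly. Leave out treatment interactions, and keep this model separate from the models that study predictors. Do not fit the 12 stratum cells.

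Two details need settling before the factors are coded:

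- Use the strata as assigned at randomisation, and add a category for children without a TMS-based class. The Transcranial magnetic stimulation section limits that test to eligible children, and a model that requires a CST class could otherwise drop the rest.
- Reconcile the HFC range. Eligibility is level 4 or above, the randomisation strata stop at 7, and the Action-observation training section has activity sets running to level 8.

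The cost is about 4 degrees of freedom (1 for HFC, 1 for age, 2 for CST class), one more if the extra CST category is used, and a few sentences of text. No new data are needed.
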